## Abstract

**Background:**

Most extremely low gestational age neonates (ELGANS, postmenstrual age at birth (PMA) < 28 completed weeks) require supplemental oxygen and experience frequent intermittent hypoxemic and hyperoxemic episodes. Hypoxemic episodes and exposure to inadequately high concentrations of oxygen are associated with an increased risk of retinopathy of prematurity (ROP), chronic lung disease of prematurity (BPD), necrotizing enterocolitis (NEC), neurodevelopmental impairment (NDI), and death beyond 36 weeks PMA.

Closed-loop automated control of the inspiratory fraction of oxygen (FiO_2_-C) reduces time outside the hemoglobin oxygen saturation (SpO_2_) target range, number and duration of hypo- and hyperoxemic episodes and caregivers’ workload. Effects on clinically important outcomes in ELGANs such as ROP, BPD, NEC, NDI and mortality have not yet been studied.

**Methods:**

An outcome-assessor-blinded, randomized controlled, parallel-group trial was designed and powered to study the effect of FiO_2_-C (in addition to routine manual control (RMC) of FiO_2_), compared to RMC only, on death and severe complications related to hypoxemia and/or hyperoxemia. 2340 ELGANS with a GA of 23 + 0/7 to 27 + 6/7 weeks will be recruited in approximately 75 European tertiary care neonatal centers. Study participants are randomly assigned to RMC (control-group) or FiO_2_-C in addition to RMC (intervention-group). Central randomization is stratified for center, gender and PMA at birth (< 26 weeks and ≥ 26 weeks).

FiO_2_-C is provided by commercially available and CE-marked ventilators with an FiO_2_-C algorithm intended for use in newborn infants. The primary outcome variable (composite of death, severe ROP, BPD or NEC) is assessed at 36 weeks PMA (or, in case of ROP, until complete vascularization of the retina, respectively). The co-primary outcome variable (composite outcome of death, language/cognitive delay, motor impairment, severe visual impairment or hearing impairment) is assessed at 24 months corrected age.

**Discussion:**

Short-term studies on FiO_2_-C showed improved time ELGANs spent within their assigned SpO_2_ target range, but effects of FiO_2_-C on clinical outcomes are yet unknown and will be addressed in the FiO_2_-C trial. This will ensure an appropriate assessment of safety and efficacy before FiO_2_-C may be implemented as standard therapy.

**Trial registration:**

The study is registered at www.ClinicalTrials.gov: NCT03168516, May 30, 2017.

## Background

Approximately 0.5% of all neonates (i.e., about 25,000 infants per year in Europe) are extremely low gestational age neonates (ELGANs), i.e. have a gestational age at birth (GA) < 28 completed weeks. The vast majority of ELGANs requires supplemental oxygen in addition to positive pressure respiratory support and frequently experience intermittent hypoxemic and hyperoxemic episodes. Intermittent hypoxemic episodes are predominantly caused by recurrent apnea due to immature development of the respiratory neuronal network (recently reviewed [1, 2]) but also secondary to active exhalation during mechanical ventilation [3]. Hyperoxemic episodes are usually a consequence of inappropriate adjustments of FiO_2_ (during routine manual control of FiO_2_ (RMC) but potentially also during closed-loop automated control of FiO_2_ (FiO_2_-C)).

### Complications of prematurity associated with recurrent hypoxemic episodes

#### Retinopathy of prematurity (ROP)

Observational data indicated that both, severe and prolonged hypoxemic episodes [4–6], and wide fluctuations in oxygen levels [7], increase the risk of ROP. Whereas a better control of SpO_2_-levels was associated with a decreased risk of ROP [8].

#### Death and neurodevelopmental impairment (NDI)

Observational studies (recently reviewed in [9]) as well as SpO_2_ data recorded during the Canadian Oxygen Trial (COT [10],) suggest that late deaths (i.e. deaths beyond 36 weeks postmenstrual age (PMA)) and NDI (both cognitive and particularly motor impairment) are linked to hypoxemic episodes, particularly those of more than 60s duration [6].

#### Necrotizing enterocolitis (NEC)

The NeOProM (Neonatal Oxygen Prospective Meta-analysis) collaboration reported a lower rate of severe NEC (defined as NEC leading to abdominal surgery or death) in infants assigned to the higher SpO_2_ target range (91–95% compared to 85–89%) [11], which was linked to a lower proportion of time spent with SpO_2_ < 80%.

### Complications of prematurity associated with hyperoxemic episodes

Considering that breathing room air (i.e., FiO_2_ = 0.21) leads to a relative hyperoxia compared to intrauterine oxygen partial pressures (PO_2_) and oxidative stress in preterm infants, hyperoxia, caused by inadequately high FiO_2_, is likely associated with long-term adverse effects [12].

#### ROP

The causal relationship between prolonged inappropriate exposure to high oxygen concentrations and ROP has long been established [13, 14]. More recently, the NeOProM studies showed increased rates of ROP with the higher SpO_2_-target range (91–95%) [11]. Finally, implementation of the higher SpO_2_-target range based on the results of the NeOProM studies, was associated with an increase in ROP rates in a recent observational study [15].

#### Death and NDI

Data from experimental studies in rodents indicate that higher levels of oxygen (e.g., FiO_2_ 0.80 for 2 to 24 h [16–18]) trigger apoptotic neurodegeneration or white matter damage in the brain. These effects have been reviewed by Back et al. [19].

#### Chronic lung disease of prematurity (BPD)

Hyperoxia enhancing generation of reactive oxygen species triggers inflammatory processes, tissue damage and cell death in the preterm infant’s lung, eventually resulting in an increased risk of BPD development (recently reviewed in [20]).

### Controlling of FiO_2_

To protect ELGANs from the detrimental effects of hypoxemic and hyperoxemic episodes, it can be assumed that PO_2_ (and in appropriate simplification SpO_2_) must be kept within a narrow target range. To achieve this goal despite the infants’ irregular breathing patterns and variations in lung aeration and function, frequent cautious adjustments of FiO_2_ are required, which are challenging, time consuming and often impossible due to limited personnel resources.

It has repeatedly been shown that FiO_2_-C increases the time infants spent within the SpO_2_-target range and reduces the burden of hyper−/hypoxemia while being safe and accurate in short-term studies (reviewed in [21, 22]). The effects of FiO_2_-C on clinically relevant outcomes measures (such as the hypoxia and hyperoxia-associated complications of prematurity described above) and the safety of its long-term continuous application, however, have yet to be elucidated.

## Methods/design

### Trial objectives

The proposed trial was designed and is powered to compare the effect of FiO_2_-C in addition to manual adjustments, in comparison with RMC of FiO_2_ only, on death, NDI and severe complications of prematurity thought to be related to hypoxia/hyperoxia in ELGANs.

### Trial design

This is an outcome-assessor-blinded, randomized-controlled, multicenter parallel group comparison of phase III for superiority (evaluating FiO_2_-C in addition to RMC of FiO_2_ in comparison to RMC of FiO_2_ only) in ELGANs.

In Germany, this study is also considered as a phase IV pharmaceutical trial on safety of the investigational medication ‘oxygen’ using different modes of administration (decision of the German authority BfArM according to §4 para. 23,1 of the German Pharmaceutical Act). This may not apply to other countries.

### Setting

Patients will be recruited in approximately 75 European tertiary care neonatal centers. Recruitment has started in Germany and is intended to expand to additional sites in other European countries, after appropriate approvals will have been obtained.

### Patients

#### Inclusion criteria

GA at birth 23 + 0/7 to 27 + 6/7 weeks

#### Exclusion criteria

Decision not to provide full life support / decision for palliative care only before study entrySevere congenital abnormalities (particularly those affecting respiratory, cardiovascular or gastrointestinal function or long-term neuro-cognitive development, whereas patent ductus arteriosus, patent foramen ovale (PFO), and atrial septal defects type II (ASDII) are not considered a congenital anomaly in preterm infants)Postnatal age > 48 hLack of parental consentLack of device enabling closed-loop automatic control of FiO_2_ before randomization

### Randomization and allocation concealment

Study participants are randomly assigned in a 1:1 ratio to FiO_2_-C in addition to RMC of FiO_2_ (test intervention) or RMC of FiO_2_ only (control intervention).

A web-based randomization tool provided by the Interdisciplinary Center of Clinical Studies at the University Medical Center of the Johannes Gutenberg University Mainz is being used in this study. This program enables bound (into the same treatment group) or free (into different treatment groups) randomization of multiples based on parental choice and the number of available devices enabling FiO_2_-C.

A minimization algorithm is applied to preferentially aim for an even distribution of treatment assignment in both GA strata (i.e. < 26 weeks and ≥ 26 weeks; 1st priority) and both gender strata (2nd priority) within each center.

### Blinding

This study is outcome-assessor-blinded, meaning that the personnel performing the ophthalmological examinations throughout the initial hospitalization as well as the personnel performing the neurocognitive evaluation at 24 months corrected age will be blinded to the infants’ treatment group assignment. Blinding of doctors, nurses, and parents is not possible with this type of study interventions.

### Study intervention

FiO_2_-C is provided by commercially available and CE marked infant ventilators with a FiO_2_-C algorithm intended for use in preterm infants. The FiO_2_-C algorithm must have been tested in human infants and shown to increase the %-time spent in the assigned SpO_2_ target range or to reduce the time in hypoxemia or hyperoxemia or to reduce the incidence/duration of hypoxemic or hyperoxemic episodes.

Each FiO_2_-C algorithm should be applied in its “optimal mode” (with respect to potentially variable settings provided by the manufacturer such as: averaging time of SpO_2_-input, response/wait-time, etc.) based on either evidence in the literature or consensus of the users.

Manual adjustments are encouraged whenever automatic FiO_2_ settings seem sub-optimal. In case of FiO_2_/SpO_2_-oscillations brought about by FiO_2_-C, settings need to be adapted or FiO_2_-C has to be temporarily interrupted.

Whenever possible, every study center will use only one type of FiO_2_-C algorithm.

Infants in the control group are treated (whenever possible) with the same type of infant ventilator for respiratory support (FiO_2_-C turned off) and RMC of FiO_2_ is applied by bedside nurse and medical staff throughout the initial hospitalization.

Care is taken in both groups that all staff are informed about the relevance of intermittent hypoxemia and hyperoxemia and trained to execute prudent and careful RMC of FiO_2_. This training may include a standard operating procedure for RMC, where the speed of increase/decrease in FiO_2_ depends on the magnitude of deviation from the SpO_2_ target range as previously described [23, 24].

The intervention should start as soon as possible after randomization and within 48 h after birth. The scheduled end of the study intervention is any of the following (whichever comes first):
deathdischarge home from hospitaltransfer to another hospital where FiO_2_-C is not available (whereas such transfer is discouraged)a PMA of 36 + 0/7 weeks*final* discontinuation of positive pressure respiratory support, which does not include limited periods without positive pressure support for weaning.
*If the infant requires positive pressure respiratory support again for any reason, the infant should again be supported by FiO*
_*2*_
*-C (provided a device supporting FiO*
_*2*_
*-C is available) until (other) criteria for scheduled end of study intervention are met.*
a PMA of > 32 + 0/7 weeks provided the following two additional criteria of respiratory stability are both met:◦ A) FiO_2_ = 0.21 for ≥48 h (for this criterion limited time periods with higher FiO_2_ for rescue or for recovery of intermittent hypoxemia will not be considered)

and
◦ B) less than 5 intermittent hypoxemic episodes with an SpO_2_ < 80% per 8 h shift.

*If criteria A) or B) are no longer met, the infant should again be supported by the FiO*
_*2*_
*-C device until (other) criteria for scheduled end of study intervention are met.*
a PMA of > 32 + 0/7 weeks if the infant has to be transferred to an intermediate care unit where FiO_2_-C is not available

*If the infant is re-admitted to intensive care, the infant should again be supported by FiO*
_*2*_
*-C (provided a device supporting FiO*
_*2*_
*-C is available) until (other) criteria for scheduled end of study intervention are met.*

After the end of the study intervention, all study participants will be treated according to the state of the art care and local standards without further requirements or restrictions.

### Concomitant interventions and medication

Any concomitant medication that is clinically considered necessary for the patient will be allowed within the study, except for the control group, where closed-loop automatic control of FiO_2_ or any other automatic control of airway pressure/respiratory support etc. based on SpO_2_ or other vital signals are not allowed.

### SpO_2_ measurements to guide FiO_2_-C

All FiO_2_-Controllers should be based on SpO_2_-data generated by the same pulse oximeter technology (Masimo). In general, pre-ductal SpO_2_-sensor placement is preferred to guide FiO_2_-C as long as echocardiography demonstrates a patent ductus arteriosus.

### SpO_2_-targets and alarm settings

The SpO_2_-target range selected by a center for clinical routine has to fulfill the following criteria:
Study centers need to have a written guideline on SpO_2_-target range to ensure that the same SpO_2_-target range is applied in both study groupsThe SpO_2_-target has to be within the range of 87–95% (may include 87% and/or 95%),Care has to be taken that the same SpO_2_-target ranges are applied in clinical routine and in both study groups

### Documentation of the study intervention

In both study groups, the type of respiratory support, the type of ventilator and the application of FiO_2_-C have to be documented daily during the intervention period on a treatment log.

### Primary outcome

The primary outcome measure is a composite of death, BPD or NEC assessed at 36 weeks PMA and severe ROP assessed when full vascularization of the retina is documented.

### Definitions of components of the primary outcome

#### Severe ROP

Defined as any ROP stage 3 or higher, or acute posterior ROP, or any ROP in Zone 1, or any treatment for ROP. ROP will be diagnosed at routine ophthalmological examinations, beginning at a PMA of 32 weeks according to international recommendations and local standards until complete vascularization of the retina [25]. The severity of ROP will be graded according to the international classification [26].

#### BPD

Defined as requiring positive pressure support or supplemental oxygen at 36 weeks ±2 days PMA, including an oxygen reduction test for infants requiring less than 0.3 FiO_2_, representing ‘moderate’ or ‘severe’ BPD according to the National Institute of Child Health and Development consensus definition [27].

#### NEC

Defined as modified Bell stage ≥IIa [28] until 36 weeks PMA.

### Co-primary outcome

The co-primary outcome (tested in a hierarchical design) is the composite outcome of death, language or cognitive delay, motor impairment, severe visual impairment or hearing impairment, all assessed at 24 ± 1 months corrected age.

### Definitions of components of the co-primary outcome

*Language or Cognitive delay:* Defined as a language or cognitive composite score at the Bayley Scales of Infant Development 3rd edition [29] of < 85.

*Motor impairment:* Defined as a Gross Motor Function Classification System (GMFCS) score of 2–5 [25].

*Severe visual impairment:* Defined as best corrected vision in the better eye yields a visual acuity less than 6/60 m (20/200 ft) according to the relevant doctor’s reports / discharge summary.

*Severe hearing impairment:* need for a hearing aid or cochlear implant.

Any clinical suspicion of previously undiagnosed visual or hearing problems during the FiO_2_-C follow-up visit requires a referral to an eye specialist or an pedaudiologist.

*If the parents refuse the assessment at the study center or if Bayley test cannot be performed:*

Other assessments of neurocognitive and motor development will betaken into account, if parents refuse to attend the follow-up.

Cognitive- and language-composite-scores will then be imputed as follows:

A score “> 85” will be imputed if
a different cognitive test has been performed elsewhere and scored higher than 1SD below the meanthe family pediatrician/doctor/health professional caring for the child or the parents rate the infant as “normal”

A score “< 85” will be imputed if
a different cognitive test has been performed elsewhere and scored lower than 1SD below the meanthe family pediatrician/doctor/health professional caring for the child or the parents rate the infant as “delayed” or “impaired”.

Any such imputation will be described in the final report and the scientific publication.

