### Sample size, power and study duration

The required sample size was calculated for the primary research hypothesis that the implementation of FiO_2_-C reduces the cumulative incidence of the composite primary outcome (death, severe ROP, BPD, or NEC).

The co-primary research hypothesis is that FiO_2_-C also reduces death or severe NDI (see outcome measures for details). These hypotheses are assessed as a-priori ordered hypotheses, where the co-primary hypothesis will only be tested in a confirmatory manner if the primary hypothesis has been confirmed. Consequently, no correction for multiple testing will be performed.

We assume that,
the cumulative incidence of the primary composite outcome of this study is 50% in the control groupFiO_2_-C reduces the burden of severe hypoxemia/hyperoxemia by 25–50% and (based on the assumption that (again) 25–50% of the outcome is associated with recurrent hypo−/hyperoxemia) effects a relative risk reduction in this outcome by at least 12.5%.

In summary, we assume a reduction in the primary outcome from 50% (in the control group) to 44% in the intervention group (FiO_2_-C).

Sample size calculations were based on a Χ^2^-test, assuming a power of 80% and a significance level of 5%. Based on these assumptions, 1110 infants are required in each treatment group (total 2220 infants). Because all components of this primary outcome will be determined during the initial hospitalization (i.e. until first discharge from neonatal care), the rate of drop-out before ascertainment of the primary outcome will be low as < 5%. Hence, a total of 2340 infants need to be enrolled and randomized (see Fig. 1).

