### Data analysis

Analysis of the primary outcome will be based on the intention to treat analysis set, which comprises all randomized patients. Portions of infants with primary endpoint will be compared in a statistical model that accounts for the factors considered by the randomization procedure and the randomization of twins and other multiples. The treatment effect will be reported as a risk ratio and as a risk difference with 95% confidence interval. The co-primary outcome will be assessed only if superiority of FiO_2_-C with respect to the primary outcome is confirmed at the 2-sided level of 0.05. This hierarchical testing procedure maintains a multiple type I error of 0.05. All statistical analyses will be described in detail in a statistical analysis plan completed before closure of the database. An interim analysis for efficacy is not intended.

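### When no Bayley result exists, the co-primary's language/cognitive component can be set by unblinded parents, takes language from a cognitive test, and can meet two opposite rules at once

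*Protocol article*

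**What the plan says.** The section on definitions of components of the co-primary outcome defines delay as a Bayley language or cognitive composite below 85. If the parents refuse the assessment or the test cannot be performed, "Cognitive- and language-composite-scores will then be imputed as follows". Two lists follow.

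- A score above 85 is assigned if "a different cognitive test has been performed elsewhere and scored higher than 1SD below the" mean, or if the family "pediatrician/doctor/health professional caring for the child or the parents rate the infant as “normal".
- A score below 85 is assigned if such a test falls below that limit, or if the same raters call the child delayed or impaired.

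The only safeguard stated is that imputations will be described in the final report and publication.

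The Blinding section says that the personnel who do the neurocognitive evaluation at 24 months are blinded. It adds: "Blinding of doctors, nurses, and parents is not possible with this type of study interventions".

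The Co-primary outcome section makes the endpoint a composite, so one component is enough for an event. Under Data analysis it is tested "only if superiority of FiO_2_-C with respect to the primary outcome is confirmed at the 2-sided level of 0.05".

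**The concern.** The co-primary is a confirmatory endpoint in a trial described as outcome-assessor-blinded. For children without a Bayley score, the rule replaces the blinded examiner with an outside test or with the opinion of people who include the unblinded parents. If parents' ratings depend even slightly on knowing which device their child had, the composite can differ between groups without any true difference, or hide a true one. Separately, the rule does not measure one of the two domains it fills in, and for some children it gives no unique answer, so someone would have to choose case by case. These faults lie in a rule that the article states. They are not details left to the analysis plan.

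**Working it through.** **Logic of the rule**

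1. *Who decides.* A child has no Bayley score and no outside test, and the parents say delayed. Both composites are set below 85, and the child is an event whatever the other components show. If the parents say normal, only the language/cognitive component is settled; death, motor, visual or hearing impairment can still make an event.
2. *Which domain.* Delay means language **or** cognition below 85, and both composites are imputed, but the only test named is a cognitive one. A child with a normal outside cognitive test, delayed language and no adverse rating is scored above 85 for language.
3. *Double assignment.* A doctor says normal and a parent says delayed. The first list is met through the doctor and the second through the parent. This conflict sits within one list item that is itself joined by *or*. If the items are alternatives, a normal outside test with a parental rating of delayed also meets both lists. No precedence is stated.

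**The plan's own figures, checked first**

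- Primary: 50% against 44%, "assuming a power of 80% and a significance level of 5"%, two-sided. This gives 1086 per group without and 1119 with continuity correction; the stated 1110 lies between them. Inflation for 5% drop-out: 2220 / 0.95 = 2337, against 2340 stated.
- Co-primary: 50% against 50% × (1 − 0.25) = 37.5%. With 20% lost, 1170 × 0.8 = 936 per group and power is 0.9998, consistent with the stated figure of more than 80%.

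**Illustration of a differential shift**

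Inputs from the document: 2340 / 2 = 1170 per group, control rate 50%, two-sided 5%. Assumptions that are not in the document: no true effect, all 1170 analysed, and a net shift *b* in the composite between groups caused by unblinded ratings.

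- SE of the risk difference = √(2 × 0.25 / 1170) = 2.07 percentage points.
- Two-sided rejection probability = Φ(−1.96 + b/SE) + Φ(−1.96 − b/SE).

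| Net shift b | Children per group | b/SE | Rejection probability |
|---|---|---|---|
| 0 | 0 | 0 | 5% |
| 1 point | 1170 × 0.01 = 11.7 | 0.48 | 7.7% |
| 2 points | 1170 × 0.02 = 23.4 | 0.97 | 16.2% |

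These probabilities apply once the primary hypothesis has been confirmed. If the primary effect is real with 80% power and the two tests are taken as independent, the unconditional figures are 0.8 × 0.077 = 6.2% and 0.8 × 0.162 = 13.0%.

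**Non-differential error**

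Assume 20% imputed, with ratings of sensitivity 50% and specificity 90%. The effect is multiplied by 1 − 0.2 + 0.2 × (0.5 + 0.9 − 1) = 0.88, so 12.5 points become 11.0. Power at 936 per group is still 0.998.

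**The case against.** The best defence is that the rule uses whatever information exists, limits missing data and will be disclosed. Multiple imputation is not free of assumptions either: if refusal depends on the child's condition, a missing-at-random model can be biased too. That stands, and it is why the present approach need not be discarded.

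Several stronger readings are tempting but not supported:

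- *That 20% of children will be imputed.* The 20% under Sample size, power and study duration is a loss-to-follow-up case used to test power. It is neither an expected figure nor a count of children scored from ratings. The document gives no such count.
- *That the bias equals the imputed share times the difference in ratings.* That is an upper bound, because another component can still make the child an event and deaths are not imputed.
- *That the trial's overall type I error becomes 8% or 16%.* The co-primary is tested only after the primary succeeds. If both null hypotheses are true, the familywise error stays at or below 5%.
- *That dilution threatens power.* It does not, as the last calculation shows.
- *That every rating professional is known to be unblinded.* The Blinding section names doctors in general. It does not mention the family paediatrician at 24 months; it only omits that role from the blinded personnel.
- *That a child with normal cognition and delayed language is always recorded as unimpaired.* An adverse rating would bring the second list into play.
- *That imputing a single fixed value is itself a finding.* How uncertainty is handled is ordinary content of the analysis plan, which is not shown.

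The list items are run together in the text as read, so a connector or ordering may have been lost. Listing the test first might be meant as precedence. That could remove the conflict between test and rating, but not the one between doctor and parent within a single item.

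**Conclusion.** The point holds in limited form. As written, the rule lets unblinded parents decide a component of a confirmatory endpoint, uses a cognitive test for language, and leaves the component undefined when raters disagree. These three conclusions rest on the text and need no numerical assumption; only the conflict between test and rating depends on reading the list items as alternatives. The size is unknown, because the share of children affected is not stated. The figures of about 8% and 16% for net shifts of 1 and 2 points are illustrative and conditional on a confirmed primary hypothesis. They show only that a shift of about 12 or 23 children per group would matter. Because the problem affects an unquantified subset of a hierarchically second endpoint, it should be fixed, but it does not undermine the trial.

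**What to change.** Reword the imputation paragraph as follows, before the database is closed:

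1. State one order of sources: a standardized outside test first; then health-care records, classified centrally without knowledge of allocation; parental rating last. A lower source is used only when no higher one exists.
2. Impute the language composite only from a language measure and the cognitive composite only from a cognitive measure.
3. Add a sensitivity analysis that treats children with only a parental rating as missing, for example by multiple imputation.

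The cost is a revised paragraph, central classification of some records and somewhat more analysis work. No new visits are needed. A few more children will lack a directly imputed score, mainly for language.
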